#### Sampling method

4.5.5

In the quantitative part of the study, convenience and continuous sampling will be implemented, in that all eligible individuals will enter the study after receiving a detailed explanation about the purpose of the study and signing an informed consent form. Afterwards, the samples will be divided into intervention and comparison groups using permuted block randomization based on Random Allocation Software considering all possible ways of assigning groups to blocks. The size of the blocks will be randomly selected (e.g., blocks containing 4, 8, 12 and 16 persons equally divided in each group). By selecting blocks randomly, the possibility of disclosing the last allocation in each block will be eliminated (Elkins, 2013; Kang et al., 2008).

This study will be an open‐label trial as masking of intervention is not possible. One of the researchers' colleagues will make the allocation sequence, and the researcher will register the participants and assign them to the intervention and control groups. All participating women will complete the initial questionnaires after randomization. The intervention group will be contacted and informed about the implementation of the intervention.

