#### Exclusion criteria

4.5.7

Adverse incidents during the studySpontaneous abortion or death of the foetus during the studyLack of motivation to cooperate with the researcher

Inclusion and exclusion criteria in the quantitative part of the study will be modified and completed after implementing the qualitative part and determining the preferred intervention.

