#### Data collection methods

4.5.9

Data from the quantitative study section will be collected using three questionnaires: the Depression, Anxiety and Stress Scale (DASS‐21), a researcher‐made questionnaire for measuring pregnant women's concerns in the process of AASTs, and demographic information and midwifery records questionnaire. The DASS‐21 and the researcher‐made questionnaire will be completed before and 8 to 10 weeks after the intervention by two groups.

The demographic information and midwifery records questionnaire has two sections: demographic‐social information and specifications of AASTs. The demographic‐social information section includes questions about age, education level, employment, economic status, year of marriage and the number of children and will be completed through face‐to‐face interviews upon entering the study. The specifications AASTs section, which will be completed 8–10 weeks after the intervention, includes questions about the timing and results of the AASTs.

The Depression, Anxiety and Stress Scale (DASS‐21) will be used to measure the emotional states of pregnant women. This questionnaire consists of 21 phrases related to the symptoms of negative emotions (depression, anxiety and stress). Each question is scored from zero (does not apply to me at all) to 3 (applies to me very much). As DASS‐21 is the abbreviated form of the main scale (42 questions), the final score of each of these subscales should be doubled. Questions 21, 17, 16, 13, 10, 5 and 3 are related to the depression subscale; questions 20, 19, 15, 9, 7, 4 and 2 are related to the anxiety subscale; and questions 18, 14, 12, 11, 8, 6 and 1 are related to the stress subscale. The validity and reliability of the DASS questionnaire for all three subscales of depression, anxiety and stress have been confirmed with the scores of 0.91, 0.84 and 0.90, respectively (Lovibond & Lovibond, 1996). The validity and reliability of this questionnaire have also been confirmed in Iran (Sahebi et al., 2005; Samani & Joukar, 2007).

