#### Data analysis

4.5.11

After completing the questionnaires, statistical analysis will be performed using SPSS16.0 on a Windows system (IBM SPSS V.16.0.0). Continuous variables will be presented in the form of mean ±standard deviation (*SD*), and categorical variables will be reported in the form of frequency (percentage). The normality of the variables will be checked using the Kolmogorov–Smirnov test. The chi‐square test or Fisher's exact test, independent sample *t* test and paired *t* test will be used to check the homogeneity of qualitative variables, compare quantitative variables between groups and compare the pre‐/posteffect in each group, respectively.

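### Baseline concern and DASS-21 scores are taken after open-label randomisation, so the 'before' measure can be influenced by the assignment

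*Protocol article*

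**What the plan says.** Section 4.5.5 (Sampling method) gives the order of events. Women enter once eligible and consented: "all eligible individuals will enter the study after receiving a detailed explanation about the purpose of the study and signing an informed consent form". Randomisation in permuted blocks follows. On masking it says "This study will be an open‐label trial as masking of intervention is not possible", and on roles it says that a colleague makes the sequence while "the researcher will register the participants and assign them to the intervention and control groups". It then fixes the timing of the baseline: "All participating women will complete the initial questionnaires after randomization". The next sentence reads "The intervention group will be contacted and informed about the implementation of the intervention".

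Section 4.5.9 (Data collection methods) names the instruments and time points: "The DASS‐21 and the researcher‐made questionnaire will be completed before and 8 to 10 weeks after the intervention by two groups". Section 4.5.10 also describes division into groups before it mentions the pre-intervention measurement.

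Section 4.5.11 (Data analysis) uses an independent t test and a paired t test to "compare quantitative variables between groups and compare the pre‐/posteffect in each group, respectively".

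Section 4.5.6 restricts entry to women whose worry about the screening process is significant, without an instrument, cut-off or time point. Section 4.5.7 adds that "Inclusion and exclusion criteria in the quantitative part of the study will be modified and completed after implementing the qualitative part" and the preferred intervention has been determined. Section 6 (Limitations) provides for the researcher to complete questionnaires by telephone for women without internet access.

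**The concern.** A baseline score is useful because the assignment cannot have affected it. Here that protection is given up by a stated choice of order. When the pre-scores are collected, the allocation exists, the researcher who made the assignment knows it, and the article describes nothing that keeps it from the woman. The instruments measure worry, depression, anxiety and stress by self-report, and answers of this kind can respond to knowledge of the arm or to the manner of an unmasked interviewer.

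Three uses of the pre-score are exposed:

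- The paired pre/post test within each group takes any shift in that group's baseline in full.
- A between-arm comparison of change, or one adjusted for baseline, takes all or part of a shift that differs between arms.
- A comparison of the groups' baseline scores can no longer separate chance imbalance from a reaction to the assignment.

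The worry criterion raises a related point. The only instrument described for concern about screening is first given in the trial after randomisation, and no earlier measure is named for a criterion that must be settled before it.

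**Working it through.** **The plan's sample size.** Section 4.5.4 gives 75 per group, 95% confidence, 80% power, d = 0.5 and 15% loss.

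n = 2(1.960 + 0.842)² / 0.5² = 62.8, so 63 per group. 63 / 0.85 = 74.1, so 75 per group. The stated figure reproduces. With 15% lost, 75 × 0.85 = 63.75 women remain, so 64 analysed per arm is used below. Using 63 changes no result by more than about 0.6 percentage points.

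**Order of events as written.** 4.5.5 gives: eligibility and consent, randomisation and assignment by the researcher, initial questionnaires, contact with the intervention group. 4.5.9 and 4.5.10 put the pre-measurement before the intervention. That is compatible with 4.5.5, but it does not place the measurement before randomisation.

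**Illustration of size.** The documents give neither a baseline shift s between arms nor a pre/post correlation r, so both are assumptions. Scores are in SD units with equal variance before and after, there is no true effect, m = 64 per arm, and tests are two-sided at 5%.

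- Change score: bias = s, SE = √(4(1 − r)/m)
- Baseline-adjusted: bias = r·s, SE = √(2(1 − r²)/m)
- Post-score only: bias = 0
- Type I error = 1 − Φ(1.96 − bias/SE) + Φ(−1.96 − bias/SE)

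For s = 0.2 and r = 0.5:

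- Change score: SE = √(2/64) = 0.177, bias/SE = 1.131, type I error 0.205.
- Baseline-adjusted: bias = 0.10, SE = √(1.5/64) = 0.153, bias/SE = 0.653, type I error 0.100.

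| r | s | Change score | Baseline-adjusted | Post-score only |
|---|---|---|---|---|
| 0.3 | 0.1 | 0.077 | 0.054 | 0.05 |
| 0.3 | 0.2 | 0.160 | 0.065 | 0.05 |
| 0.3 | 0.3 | 0.300 | 0.083 | 0.05 |
| 0.5 | 0.1 | 0.087 | 0.062 | 0.05 |
| 0.5 | 0.2 | 0.205 | 0.100 | 0.05 |
| 0.5 | 0.3 | 0.396 | 0.165 | 0.05 |
| 0.7 | 0.1 | 0.113 | 0.086 | 0.05 |
| 0.7 | 0.2 | 0.309 | 0.198 | 0.05 |
| 0.7 | 0.3 | 0.591 | 0.384 | 0.05 |

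**The paired test that 4.5.11 names.** In an arm whose baseline alone is shifted by s, with no true change over time, bias = s and SE = √(2(1 − r)/m). For s = 0.2:

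- r = 0.5: SE = √(1/64) = 0.125, bias/SE = 1.60, false-positive rate about 0.36.
- r = 0.7: SE = √(0.6/64) = 0.097, bias/SE = 2.07, false-positive rate about 0.54.

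The rates are the same for a shift in either direction. A shift of 0.2 SD is 0.2/0.5 = 40% of the planned effect.

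**The case against.** Several points on the other side are sound.

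- **Women's knowledge of their arm.** The article does not say that women know their arm when they complete the baseline. Contact with the intervention group comes in the following sentence, so some may answer first. This stands: only the researcher's knowledge is certain. But the sentence order is not a safeguard, and no concealment from the women is stated.
- **Who collects the data.** A reader might infer that the assigning researcher administers all the questionnaires. The article documents this only for women without internet access. The face-to-face interviews in 4.5.9 concern the demographic items.
- **The analysis.** 4.5.11 names neither a change-score test between arms nor a baseline-adjusted analysis, and an independent t test on post-scores is untouched by a baseline shift. This stands and limits the damage. It leaves the named paired tests exposed, and the section does not say which scores the independent t test will compare.
- **Direction.** Relief in the intervention arm and disappointment among controls would lower the intervention baseline relative to control and work against the intervention. The direction is unknown, so the claim is one of possible bias, not of bias in favour.
- **The worry criterion.** A stronger reading is that worry is judged on the post-randomisation questionnaire and women are then removed. The documents do not support it. 4.5.5 and 4.5.10 place eligibility and consent before randomisation, no exclusion in 4.5.7 rests on a baseline score, and the criteria are still to be completed. A separate screen before consent would satisfy every section. What remains is that no pre-randomisation measure of worry is described.

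**Conclusion.** The concern holds for the baseline scores. That they are taken after open-label randomisation, by which point the assigning researcher knows the arm, is stated outright and is not a detail left to a fuller document. The pre-scores can therefore be influenced by the assignment. That would bias the paired pre/post tests and any change-score or baseline-adjusted comparison, and would blur a baseline comparison of the scores. A post-score comparison between arms would not be biased by this route.

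The size cannot be taken from the documents. The rates above show only that a modest shift would matter: at 0.2 SD with r between 0.5 and 0.7, about 20% to 31% for change scores and 10% to 20% after baseline adjustment. With a 0.1 SD shift and r = 0.3, the same figures are 7.7% and 5.4%.

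On the worry criterion, the documents support a request for clarification and nothing stronger.

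**What to change.** In 4.5.5, replace the sentence on the initial questionnaires with: 'All participating women will complete the initial questionnaires after consent and before randomisation, and before the allocation is revealed to the researcher or the participant.' Align 4.5.10 with this order.

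When the entry criteria are completed as 4.5.7 foresees, state that worry is assessed and eligibility confirmed before randomisation, and that no woman is removed afterwards on her baseline score. The tool can be settled then. If the concern questionnaire itself is chosen, a cut-off will be needed, and the content validation and test–retest work in 4.5.9 will not supply one. Selecting women on high scores would also add regression to the mean to the paired tests.

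The cost of the reordering is small. The same forms are completed one step earlier and the sample size stays at 75 per group. Some women may complete a form and then not be randomised. The change has to be made before recruitment starts, because a baseline free of the assignment cannot be recovered afterwards.

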#### Inclusion criteria

4.5.6

Pregnant women with a gestational age of fewer than 11 weeks that apply for completing the initial prenatal recordLack of Down syndrome and other anomalies in the foetus in previous pregnanciesNo history of known mental disorders or consumption of psychiatric drugsPregnant women with a significant level of worry about AASP

#### Exclusion criteria

4.5.7

Adverse incidents during the studySpontaneous abortion or death of the foetus during the studyLack of motivation to cooperate with the researcher

Inclusion and exclusion criteria in the quantitative part of the study will be modified and completed after implementing the qualitative part and determining the preferred intervention.

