#### The implementation method

4.5.10

The quantitative part of the study is a randomized controlled trial to determine the impact of the designed intervention on reducing pregnant women's concerns for undergoing AASTs. After registering the study in the Iranian Registry of Clinical Trials (IRCT), obtaining the necessary approval from the School of Nursing‐Midwifery and the Ethics Committee and presenting the recommendation letter to hospitals and health centres, affiliated with Tehran University of Medical Sciences, sampling will start at these centres. Initially, continuous convenience sampling will be implemented, that is, all eligible pregnant women will be enrolled in the study after receiving detailed explanations about the purpose of the study, and signing a written consent form. Next, the samples will be divided into intervention and comparison groups using permuted block randomization. The designed intervention will be presented for the intervention group. The control group will not receive any interventions from the research team during the study. Before and 8–10 weeks after the intervention, the status of the participants in the intervention and control groups will be measured using the questionnaire. Finally, the results before and after the intervention will be analysed using inferential statistical methods. A telephone follow‐up will be performed to ensure that all intervention participants receive the intervention and also to ensure the completion of questionnaires in both groups. The participants' data will be stored on a computer and kept confidential. Each participant will have a unique code to avoid double data entry. Participants will be assured of the confidentiality of information.

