## DISCUSSION

5

According to the guidelines of the American College of Obstetrics and Gynecology, screening for aneuploidy should be the patient's informed choice while providing help for her to make a decision based on clinical conditions, values, interests and goals. The purpose of a screening test is to provide information, not to dictate a process (ACOG & May, 2016).

Screening tests are routinely requested for all pregnant women in Iran. If a midwife or gynaecologist does not request a screening test and the baby is born with Down syndrome, there will be legal ramifications (Abbasi et al., 2012). Given the limited time required for legal abortion in Iran (until 18 WK and 6 days of gestational age), these tests are requested promptly with no time devoted to training. Due to the high cost of the tests, individuals refuse to undergo the tests if they are not provided with proper information.

A screening test is a method that can identify seemingly healthy people who are at high risk for a disease or disorder, yet there is no guarantee that it will not occur. The majority of high‐risk women receive normal diagnostic results. Therefore, the unreasonable concern is the main psychological and social cost that these women pay for screening tests. Consequently, exceptional attention should be paid to concerns associated with AASTs. Promoting professional support during these phases might help control and manage these concerns and associated distress. Therefore, the researcher intends to design an appropriate and comprehensive intervention to provide the necessary conditions for mothers to make informed decisions and reduce their concerns in the AASP. As women's health concerns are culture‐ and context‐based and cannot be assessed by quantitative research alone, the research team will conduct a multi‐phased study. First, we will examine women's concerns about AASTs using a qualitative approach. Afterwards, using the experiences of these women and the experts' opinions, we will offer an intervention to reduce their concerns in one of the most critical stages of their lives. The results of this study can serve as a basis for policy‐making and interventional strategies in healthcare systems to alleviate pregnant women's concerns and improve their mental health by providing knowledge about their concerns in AASTs.

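### The trial's exclusion criteria include events after randomisation and an untimed cooperation criterion, so randomised women can be removed for reasons that may depend on arm or outcome

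*Protocol article*

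**What the plan says.** Section 4.5.7 of the protocol article gives three exclusion criteria for the trial, which run together in the extracted text: "Adverse incidents during the studySpontaneous abortion or death of the foetus during the studyLack of motivation to cooperate with the researcher". The first two are tied to the period of the study. The third has no time attached.

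Section 4.5.5 sets the order of events: "all eligible individuals will enter the study after receiving a detailed explanation about the purpose of the study and signing an informed consent form". Randomisation comes after that, and the baseline questionnaires come after randomisation. On masking and roles the same section says "This study will be an open‐label trial as masking of intervention is not possible" and "the researcher will register the participants and assign them to the intervention and control groups".

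Section 4.5.9 fixes the measurement times: "The DASS‐21 and the researcher‐made questionnaire will be completed before and 8 to 10 weeks after the intervention by two groups". The timing and results of the screening tests are recorded at the later point. Section 4.5.10 says of the comparison arm: "The control group will not receive any interventions from the research team during the study". It also plans telephone contact, to check that the intervention is received in the intervention arm and that questionnaires are completed in both arms.

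Section 4.5.7 ends by declaring its lists provisional: "Inclusion and exclusion criteria in the quantitative part of the study will be modified and completed after implementing the qualitative part".

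**The concern.** An exclusion criterion normally decides who may be randomised. Here at least two of the three act on women who are already in the trial. If they are followed as written, the groups compared at 8 to 10 weeks are those left after removal, not those formed by randomisation.

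Two items call for particular care.

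- **Cooperation.** The person with whom the woman must cooperate also assigns the arms, and nobody is masked. Intervention women have a programme to take part in as well as questionnaires; controls have only questionnaires. Removal for poor cooperation can therefore differ between arms. Because baseline questionnaires follow randomisation, even early reluctance may reflect knowledge of the arm.
- **Adverse incidents.** The term is undefined and stands apart from pregnancy loss, so it must mean something else. Women enter before 11 weeks, and the Introduction places the screening tests between 11 weeks and 16 weeks 6 days, so results can arrive while the rule applies. The Discussion says of high-risk women whose diagnostic results are mostly normal: "Therefore, the unreasonable concern is the main psychological and social cost that these women pay for screening tests". If an adverse screening course were counted as an incident, the trial would lose women central to its third-stage objective.

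**Working it through.** **Step 1. The plan's own figure.** Inputs from section 4.5.4: 95% confidence (taken as two-sided 5%), 80% power, d = 0.5, 15% loss.

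- n = 2 × (1.960 + 0.842)² / 0.5² = 62.8, so 63 per group.
- 63 / 0.85 = 74.1, so 75 per group. The t-test version gives 63.77 / 0.85 = 75.02.

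The stated 75 is reproduced. Power at d = 0.5 (t test) is 0.86 with all 75 per group measured and 0.80 with 64.

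**Step 2. Do the criteria act after randomisation?** Section 4.5.5 puts consent and entry before allocation. An event during the study can therefore happen to an allocated woman, and the first two items fit that description. The third is untimed. Its place in a list of during-study events suggests use during the study. For the qualitative stage, section 4.2.3 lists willingness to participate as an inclusion criterion, which shows how an entry condition was worded there. Neither point is decisive.

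**Step 3. How large could the effect be?** The document gives no removal rates, so everything here is assumed: no true effect, 75 randomised per arm, two-sided 5% test, higher score = more concern. The 15% is the planned loss allowance, used as a ceiling. Section 4.5.4 does not assign it to one arm.

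*Model A: the least motivated fraction f is removed from the intervention arm only. Lack of motivation correlates r with the follow-up score.*

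Shift = r × φ(z) / (1 − f), with z the upper-f normal quantile. The rejection rate uses shift / √(1/(75(1 − f)) + 1/75).

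| f | r | Shift (SD) | Share of d = 0.5 | Type I error |
|---|---|---|---|---|
| 5% | 0.5 | 0.05 | 11% | 6.2% |
| 15% | 0.3 | 0.08 | 16% | 7.7% |
| 15% | 0.5 | 0.14 | 27% | 12.7% |

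For f = 15%: φ(1.036) / 0.85 = 0.233 / 0.85 = 0.274. Times 0.5 this is 0.137, and 0.137 / 0.170 = 0.80. At r = 1 the shift is 0.27 SD and the error 36%, but motivation would then have to be identical to the outcome, so this is only a mathematical bound.

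*Model B: 20% of women in each arm have a bad course that raises their score by m SD (m = 0.5 to 1), and all removals come from this group.*

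After removing f, the share with a bad course among those kept is (0.20 − f) / (1 − f): 0.200 at f = 0, 0.158 at 5%, 0.111 at 10%, 0.059 at 15%. The shift is m times the difference between arms. Type I error comes from 8,000 simulated trials per setting.

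| Removed, intervention v control | Shift (SD) | Type I error |
|---|---|---|
| 15% v 0% | 0.141m: 0.07 to 0.14 | 6.8% to 12.1% |
| 15% v 5% | 0.099m: 0.05 to 0.10 | 6.4% to 8.6% |
| 10% v 5% | 0.047m: 0.02 to 0.05 | 5.1% to 5.7% |
| 15% v 15% | 0 | 4.9% to 5.2% |

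Runs with no removal gave 5.4% and 5.8%, so the 10% v 5% row cannot be told apart from no inflation.

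**The case against.** Much of the case on the other side stands.

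- **High-risk results.** A reader might infer that women with a high-risk result or a found anomaly will be dropped as adverse incidents. The document does not say so. Section 4.5.9 plans to record test results at follow-up, which fits keeping women whatever the result. What remains is that the term is undefined and can be read either way.
- **Motivation.** A reader might infer that this item is certainly applied after randomisation. It has no time stamp and could be an entry condition. The comparison with section 4.2.3 is weak, because that list belongs to the qualitative stage.
- **Direction.** A reader might infer a bias towards benefit. That holds only if removal falls mainly on intervention women with poor scores. The wording concerns cooperation with the researcher, not with the intervention, and controls also have questionnaires to complete. Controls who are offered nothing might disengage more, and women with little concern might be the least motivated. Either could weaken or reverse the bias.
- **Provisional criteria and analysis set.** The criteria are still to be completed, and an analysis set is commonly left to a fuller plan. But a promise to modify the lists does not withdraw these items. The point rests on what section 4.5.7 states, namely during-study events as grounds for exclusion, and not on the absence of an analysis-set definition.

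**Conclusion.** The point holds in this limited form. Section 4.5.7 presents post-randomisation events as exclusion criteria in an open-label trial, with one term undefined and one item untimed. Followed as written, it allows randomised women to be removed for reasons that may depend on arm or outcome.

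The size is not established by the document. Under the assumptions shown, one-sided removal of 15% would matter: about 0.07 to 0.14 SD against a planned 0.5 SD, with a type I error of about 7 to 13% across both models. A slight imbalance (10% v 5%) would hardly matter. Equal removal by the same mechanism gives no bias when there is no effect, but the result then under-represents women whose course was bad. The text does not support saying that the trial's result will be biased, or that it will favour the intervention.

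**What to change.** When the provisional criteria are completed:

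1. Keep as exclusion criteria only conditions assessed before randomisation. Willingness to cooperate can be one of them if it is judged before allocation.
2. Delete adverse incidents during the study, and lack of motivation arising after randomisation, as reasons to exclude randomised women.
3. Seek the 8-to-10-week questionnaires from every randomised woman, including those who stop the intervention or receive a high-risk result, and analyse each in her allocated arm.
4. Where the pregnancy has ended and the concerns questionnaire can no longer apply, record the event and its reason and report these by arm beside the main result.

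The cost is a change of wording. Telephone follow-up for questionnaires is already planned in both arms (section 4.5.10), and 75 per group already carries the 15% loss, so the sample size stays the same. The small downside is that the estimated effect may be somewhat smaller, because women who do not engage are counted.
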